# A multicenter prospective randomized study comparing the incidence of periprocedural cerebral embolisms caused by catheter ablation of atrial fibrillation between cryoballoon and radiofrequency ablation (Embo‐Abl study): Study design

**DOI:** 10.1002/clc.23949

**Published:** 2022-11-22

**Keywords:** atrial fibrillation, cerebral embolism, cryoballoon ablation, radiofrequency ablation

## Abstract

**Background:**

Although catheter ablation (CA) has become a standard therapeutic approach to atrial fibrillation (AF), it imposes a low but relevant risk of thromboembolic complications of around 0.5%–1%, including ischemic strokes, and has an additional risk of clinically silent cerebral embolisms (SCEs) of 10%–40%. Both cryoballoon (CB) and radiofrequency (RF) ablation are routinely used clinically worldwide, yet there are few prospective data comparing the incidence of cerebral embolism after CA of AF between CB and RF ablation.

**Methods:**

The aim of the Embo‐Abl study will be to compare the incidence of cerebral embolisms on 3 T diffusion‐weighted image magnetic resonance imaging (MRI) after CA of AF between CB and RF ablation in patients with AF in a prospective, multicenter, open‐label, controlled, randomized fashion. The primary endpoint of the Embo‐Abl study will be the occurrence of MRI‐detected SCE 1–3 days after CA. The patients will be registered and randomly assigned to either the CB or RF ablation group in a 1:1 ratio. The study cohort will include 230 patients with AF from a multicenter in Japan.

**Results:**

The results of this study are currently under investigation.

**Conclusion:**

The Embo‐Abl study will be the first to compare the incidence of periprocedural cerebral embolisms caused by CA of AF between CB and RF ablation in a prospective, multicenter, randomized, controlled fashion.

AbbreviationsACTactivated clotting timeADCapparent diffusion coefficientAEadverse eventAFatrial fibrillationATatrial tachyarrhythmiaBPblanking periodCAcatheter ablationCBcryoballoonCRBCertified Review BoardCRFCase Report FormDOACdirect oral anticoagulantsDSMBData and Safety Monitoring BoardDWIdiffusion‐weighted imageFLAIRfluid‐attenuated inversion recoveryjRCTJapan Registry of Clinical TrialsLAleft atriumLAAleft atrial appendageLADleft atrial dimensionMESmicroembolic signalPAFparoxysmal atrial fibrillationPeAFPersistent atrial fibrillationPVpulmonary veinPVIpulmonary vein isolationRFradiofrequencySCEsilent cerebral embolismSCLsilent cerebral lesionTCDtranscranial Doppler

## INTRODUCTION

1

Atrial fibrillation (AF) is the most common arrhythmia in clinical practice and the prevalence of AF in the general population is increasing rapidly.^1^, ^2^ AF markedly increases the risk of ischemic strokes and death, and furthermore, it has been reported to be independently associated with cognitive dysfunction as well.^3^, ^4^, ^5^

Catheter ablation (CA) has become a standard therapeutic approach to AF.^2^ CA of AF can improve the quality of life of patients by maintaining sinus rhythm, and further, some observational studies have shown that AF ablation decreases the risk of ischemic strokes and death.^6^ Therefore, AF ablation has been increasingly performed worldwide. On the other hand, CA of AF imposes a low but relevant risk of thromboembolic complications of around 0.5%–1% including ischemic strokes, and has an additional risk of clinically silent cerebral embolisms (SCEs) of 10%–40%.^2^, ^7^, ^8^, ^9^ Although the mechanisms of the SCEs caused by CA of AF and its clinical impact are not fully understood, some studies have reported that SCEs could be a marker of procedure‐related clinical stroke risk, and cerebral microinfarctions due to those cerebral embolisms could contribute to cognitive dysfunction.^4^, ^10^, ^11^

Electrical pulmonary vein isolation (PVI) is the cornerstone of any AF ablative procedure not only for paroxysmal atrial fibrillation (PAF) but persistent atrial fibrillation (PeAF).^2^ Although the most widely adopted and established technique for AF ablation is radiofrequency (RF) ablation, the efficacy of CA in fact depends on the operator's experience, especially in cases of RF ablation.^12^ Recently, cryoballoon (CB; Arctic Front Advance, Medtronic) ablation has emerged to simplify the PVI and has also become a widely accepted strategy for CA of AF.^13^, ^14^, ^15^

Because there are fundamental differences in the two technologies of CB and RF ablation both in the energy form and energy delivery, the type and incidence rate of CA‐related complications differ between CB and RF ablation. There are few prospective data comparing the incidence of cerebral embolism after CA of AF between CB and RF ablation.

## METHODS

2

### Aim

2.1

The aim of the Embo‐Abl study is to compare the incidence of cerebral embolisms on 3 T diffusion‐weighted image (DWI) magnetic resonance imaging (MRI) after CA of AF between CB and RF ablation in patients with AF in a prospective, multicenter, open‐label, controlled, randomized, noninferiority fashion.

### Primary hypothesis and study design

2.2

The primary hypothesis of the Embo‐Abl study is that CB ablation is not inferior to RF ablation with respect to the incidence of cerebral embolisms after the CA of AF. The Embo‐Abl study is designed as a prospective, multicenter, open‐label, controlled, randomized, noninferiority clinical study comparing the incidence of periprocedural cerebral embolisms between CB and RF ablation of AF from April 28, 2021 to March 31, 2028 (Figure 1). The enrollment period will be from April 28, 2021 to March 31, 2025. The study cohort will include 230 patients with AF from a multicenter in Japan. The enrollment and study periods will be extended if the number of enrolled patients is not achieved during the period, and it will be shortened if the number of enrolled patients is achieved earlier.

**Figure 1 clc23949-fig-0001:**
[figure not shown]
Flowchart of the study. MRI, magnetic resonance imaging.

### Primary endpoint

2.3

The primary endpoint of the Embo‐Abl study will be the occurrence of MRI‐detected SCEs 1–3 days after CA.

### Secondary endpoints

2.4

The key secondary endpoints are defined as follows:

*Safety analysis*:
1.Occurrence of silent cerebral lesions (SCLs) by brain MRI 1 to 3 days after CA of AF.2.Occurrence of SCEs or SCLs by brain MRI 1 month after CA of AF.3.Number of microembolic signals (MESs) during CA of AF.4.Microbleeds detected by brain MRI 1 to 3 days and 1 month after CA of AF.5.Complications following CA of AF.

*Efficacy analysis*:
1.The success rate of CA of AF during the acute phase.2.Recurrence of atrial tachyarrhythmias (ATs) at 1 year after CA with a blanking period (BP) of 90 days after CA of AF.

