#### Postoperative brain MRI

2.6.4

Brain MRI will be acquired 1–3 days after the index ablation procedure using a 3 T scanner (MAGNETOM Prisma, Siemens Healthineers; MAGNETOM Vida, Siemens Healthineers; SIGNA Premier, GE Healthcare; Ingenia Elition, Philips Healthcare) with a six‐channel body array coil. The imaging protocol will consist of DWI, T2‐weighted axial fluid‐attenuated inversion recovery (FLAIR), and T2* (T2 star) sequences. The sequence parameters are described in the Supporting Information: Table.

For each DWI sequence, the apparent diffusion coefficient (ADC) map will be obtained to prevent overdetection of T2 shine‐through effects on the DWI. The slices and orientation of the DWI and FLAIR sequences will be matched to evaluate the correlation between the DWI and FLAIR images.

The number, localization, and size of the SCEs/SCLs will be analyzed.

According to the latest recommendations, SCEs/SCLs were defined as below:^7^
1.SCE = diffusion positive (DWI hyperintense) + ADC reduced and2.SCL = diffusion positive (DWI hyperintense) + ADC reduced + FLAIR positive.

Patients with new embolic lesions on the postprocedural MRI will undergo a follow‐up MRI 1 month after CA to assess the lesion progression. Microbleeds will be identified and counted as nodular, strongly hypointense lesions on either the T2*‐weighted or susceptibility‐weighted imaging. All brain MRI images will be independently evaluated by certified radiologists ([name] and [name]) blinded to the patient characteristics and ablation technology used. If the SCEs and/or SCLs are detected on brain MRI, a neurologist or cardiologist who has been trained in neurology will assess the neurological findings and determine whether they are symptomatic or asymptomatic.

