### Sample size and power

2.8

The targeted sample size is 230 (115 in each group). The sample size was calculated based on the primary hypothesis. The rate of MRI‐detected SCEs after CA of AF has been reported to be comparable between CB and RF ablation, ranging from 10% to 30% in the observational studies.^7^ Based on those data, a rate of MRI‐detected SCEs of 20% in both groups is assumed. The noninferiority hypothesis will be evaluated with a noninferiority margin of 15%. The sample size is calculated as 112 patients per group with a power of 80% based on a significance level of 5%. To cope with a potential loss‐to‐follow‐up, a minimum of 230 patients (115 patients per group) will be enrolled in this study.

When the primary endpoint is observed in half of the total sample size (116 patients), early stopping of the study for futility will be considered based on the conditional power at an interim analysis, which will be reviewed by the Data and Safety Monitoring Board (DSMB). A simulation suggested a very limited power loss with a potential early stopping for futility, and the targeted power is expected to be achieved with this sample size.

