## LIMITATIONS

5

We will not acquire brain MRI before CA in this study, and therefore, it is possible that postprocedural SCEs/SCLs may occur preprocedural. However, we think that is highly unlikely because acute cerebral lesions will be defined on 3 T DWI, which is positive only a few weeks after a cerebral embolism, and actually, acute cerebral lesions were found in none of the previous studies that assessed preprocedural MRI in patients who underwent CA of AF.^35^

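### The 1-month SCE/SCL endpoint keeps the acute DWI and ADC criteria, so it cannot tell a resolved lesion from one that has only lost its DWI signal

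*Protocol article*

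**What the plan says.** Section 2.4 of the protocol article includes among the key secondary safety endpoints "Occurrence of SCEs or SCLs by brain MRI 1 month after CA of AF".

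Section 2.6.4 is the only place where the two terms are defined: "SCE = diffusion positive (DWI hyperintense) + ADC reduced", and "SCL = diffusion positive (DWI hyperintense) + ADC reduced + FLAIR positive". No separate version for the later scan is given. The same section states who has that scan and why: "Patients with new embolic lesions on the postprocedural MRI will undergo a follow‐up MRI 1 month after CA to assess the lesion progression".

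Section 5 (Limitations) explains why no MRI is done before ablation. Acute lesions are identified on DWI, "which is positive only a few weeks after a cerebral embolism".

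**The concern.** The criteria describe a fresh lesion, and the endpoint applies them about four weeks later. By the article's own account one of the two required signals is short-lived. A lesion that leaves a lasting FLAIR abnormality after its DWI signal has gone is then neither an SCE nor an SCL at 1 month. That residual lesion is what a scan for lesion progression should pick up.

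The stake is a key secondary safety result that is hard to interpret. Few or no cases at 1 month could mean that lesions healed, or only that the acute signal faded. A real difference between cryoballoon and radiofrequency ablation in lasting lesions could go unseen.

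**Working it through.** **Inputs**
- Acute SCE rate: "a rate of MRI‐detected SCEs of 20% in both groups is assumed" (section 2.8). The same section cites observational rates of 10% to 30%.
- Patients per arm: 115 (section 2.8).
- Rescanned at 1 month: only patients with new lesions at 1–3 days (section 2.6.4).
- q, the share of lesion-positive patients with at least one lesion still DWI positive with reduced ADC at 1 month: not in the documents. Assumed range 0% to 50%.

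**The plan's own figure.** The article gives no figure for the 1-month endpoint. Its one related figure, 112 per group for the primary test, reproduces with a two-sided 5% level: (1.960 + 0.842)² × 2 × 0.20 × 0.80 / 0.15² = 111.6, rounded up to 112. The 20% used below is thus the rate on which the trial was sized.

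**Step 1: apply the definitions at 1 month.** A lesion seen at 1–3 days can be in one of four states:

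| State at 1 month | DWI positive and ADC reduced | FLAIR | SCE | SCL | Endpoint |
|---|---|---|---|---|---|
| Acute signal and FLAIR lesion | yes | positive | yes | yes | counted |
| Acute signal only | yes | negative | yes | no | counted |
| FLAIR residual only | no | positive | no | no | not counted |
| Vanished | no | negative | no | no | not counted |

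The last two rows score the same. The FLAIR column never changes the last column, so naming SCL alongside SCE adds no patient to the endpoint. This step needs no outside figure.

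**Step 2: patients rescanned.** 115 × 0.20 = 23 per arm (11.5 at a 10% rate, 34.5 at 30%).

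**Step 3: expected cases.** Cases per arm = 115 × 0.20 × q. Rate = 0.20 × q. Probability of no case in the whole trial = (1 − 0.20q)^230.

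| q (assumed) | Cases per arm | Rate | P(no case in trial) |
|---|---|---|---|
| 0% | 0 | 0% | 100% |
| 5% | 1.2 | 1.0% | 10% |
| 10% | 2.3 | 2.0% | 1% |
| 20% | 4.6 | 4.0% | below 0.1% |
| 50% | 11.5 | 10.0% | below 0.1% |

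The rate is 2% or less only if q is 10% or lower.

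**Step 4: what could be lost (illustration only).** Suppose that 25% of lesion-positive patients in one arm and 75% in the other have a lasting lesion. On 115 per arm this is 5% versus 15%.
- Persistence definition: power = Φ[(0.10 − 1.96 × 0.0396) / 0.0390] ≈ 72%. The two standard errors are the pooled and the unpooled one.
- Acute definition, if 5% to 10% of those patients still meet DWI and ADC: expected cases are 0.3 versus 0.9 up to 0.6 versus 1.7 per arm, and power is about 8% to 12%.

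The contrast is deliberately large, both inputs are assumptions, and the normal approximation is crude with so few cases. The example shows the direction of the loss. It does not forecast its size.

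**The case against.** Four points can be made for the plan.

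- *The timing remark is loose.* It was written to defend omitting a preprocedural scan, gives no number of weeks, and a few weeks runs close to 1 month. It also covers DWI only; the article does not say how long ADC stays reduced. This stands against any firm forecast. It does not rescue the definition: the two criteria are required together, so loss of DWI alone removes a lesion from the count.
- *The definitions may be meant for the early scan only.* They appear in the account of the 1–3 day MRI, and the later scan has its own stated purpose. But section 2.4 uses the same two terms for the 1-month endpoint, and the article offers no other meaning for them.
- *The analysis plan can settle it.* It can, and that is a good place for the repair. Still, this is not just a detail left for later: the article states a rule, and following it literally gives the wrong count.
- *Only a secondary endpoint is touched.* This is correct and limits the severity.

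A reader might go further and infer that the endpoint must be near zero in both arms whatever the true persistence, or that the remaining positives would mostly be new emboli. The documents support neither. The first depends on q, which is not given; at 20% to 50% the count is 4.6 to 11.5 per arm. On the second the article is silent.

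**Conclusion.** The concern holds as a moderate one. The 1-month endpoint has no definition suited to 1 month. Under the only definitions given, a FLAIR-positive, DWI-negative residual is scored as no lesion, so resolution and fading of the acute signal cannot be separated. That conclusion follows from sections 2.4, 2.6.4 and 5 read together and needs no assumption about rates.

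The size does need one. With about 23 rescanned patients per arm, the expected count runs from 0 to 11.5 as the assumed q runs from 0% to 50%. A low rate is likely, given what the article says about DWI, but it is not established. The primary endpoint at 1–3 days, its margin and its sample size are not affected.

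**What to change.** Give the 1-month endpoint its own definition: FLAIR hyperintensity at the site of a lesion that was DWI positive with reduced ADC at 1–3 days, regardless of DWI and ADC status at 1 month. Report any new DWI/ADC-positive lesion at 1 month as a separate item, noting that it can be found only among the patients who are rescanned. State the denominator at the same time (all patients in the arm, or those with a lesion at 1–3 days).

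The cost is one definition and one added field on the reader form. FLAIR is already in the imaging protocol with slices matched to DWI, so no further scan, sequence or reader is needed. One small drawback remains: without a preprocedural MRI, an older FLAIR lesion at the same site could be counted as a residual. The definition should acknowledge this.

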### Inclusion and exclusion criteria

2.5

#### Inclusion criteria

2.5.1

Subjects must meet all the following criteria:
1.Diagnosed with AF with at least one episode documented (≥30 s) in accordance with the 2014 AHA/ACC/HRS guidelines.^2^
2.Planned RF or CB ablation of AF.3.Age 20–85 years.4.Capable of complying with the protocol and providing written informed consent.

#### Exclusion criteria

2.5.2

Those who meet any of the following criteria are ineligible for the study:
1.History of AF ablation or cardiac surgery.2.Left atrial dimension (LAD) > 55 mm (parasternal long‐axis view in transthoracic echocardiography).3.Inability to undergo a brain MRI.4.Women are currently or possibly pregnant.5.Concomitant participation in another intervention study.6.Patients whom doctors responsible for this study judge to be inappropriate.

### Interventions

2.6

#### Study procedures

2.6.1

Transesophageal echocardiography and/or contrast CT will be performed before the CA procedure in all patients to exclude the presence of any thrombi in the left atrial appendage (LAA) and left atrium (LA). All antiarrhythmic drugs except for amiodarone will be discontinued for at least five half‐lives. All patients will receive oral anticoagulants for at least 3 weeks before the CA procedure. Warfarin will be continued throughout the pre‐ and postprocedural period. Direct oral anticoagulants (DOACs) such as apixaban, rivaroxaban, dabigatran, or edoxaban will be continued throughout the pre‐ and postprocedural period, or the dose will be withheld on the day of the ablation procedure and will be resumed on the evening of the CA procedure or on the morning of the next day according to the hospital's standard strategy. The levels of the coagulation markers such as the prothrombin time, activated partial thromboplastin time, d‐dimer, thrombin‐antithrombin III complex, soluble fibrin monomer complex, and blood concentration of the DOACs will be measured before the CA procedure as preoperative samples, and 1–3 days after the procedure.

During the CA procedure, intravenous heparin will be introduced to maintain an activated clotting time (ACT) of 300–400 s during the procedure. The ACT will be monitored every 15 min. The esophageal temperature will be monitored with a temperature probe (SensiTherm Multi, Abbott; Esophastar, Japan Lifeline; Circa, Boston Scientific). A PVI will be mandatorily performed in both groups. Confirmation of LA to the pulmonary vein (PV) electrical connection and PVI will be conducted with a circular (Achieve, Medtronic, Lasso, Biosense Webster; Advisor, AFocus, Optima, Abbott; EP star Libero, Japan Lifeline), PentaRay (Biosense Webster), or HD grid (Abbott) catheter at a proximal site in the ostium in each vein before and after the ablation. Exit block from each PV is also confirmed after PVI by pacing from the circular, PentaRay, or HD grid catheter within the PV.

A cavotricuspid isthmus ablation will be performed in patients who have clinical or inducible cavotricuspid isthmus‐dependent atrial flutter. Other adjunctive ablation lesion sets targeting sites outside the PVs will be conducted when non‐PV AF triggers are detected and/or atrial tachycardias are induced.

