### Statistical analysis

2.11

For the primary endpoint, safety analyses will be performed based on the intention‐to‐treat principle. A per‐protocol basis analysis will also be performed as a supplemental analysis. When noninferiority is demonstrated on the primary endpoint, the superiority hypothesis will also be evaluated. An asymptotic method based on the normal distribution will be used to compare the rate of SCEs by brain MRI 1–3 days after CA of AF.

Other categorical variables will be presented as absolute and relative frequencies and compared using a chi‐square test or Fisher's exact test. Continuous variables will be presented as the mean ± standard deviation for normally distributed data or median with the interquartile range (25th–75th percentiles) for skewed data and analyzed with the Student's *t*‐test or Wilcoxon rank‐sum test, as appropriate. If RF catheters are used in the CB ablation group for touch‐ups, we plan to carry out analyses that include both patients with touch‐ups and that excludes those without touch‐ups, respectively.

A *p* < .05 will be considered statistically significant. Logistic regression analyses and multivariable Cox regression analyses will be performed to investigate the predictors associated with clinical outcomes. Statistical analysis will be performed using up‐to‐date versions of the Stata software (StataCorp). The patient demographic data and outcomes of the CA in each group will be collected descriptively as presented in Tables 1 and 2. A detailed plan for the interim analysis and final analysis will be prespecified in the statistical analysis plan, which will be prepared and finalized before the database lock.

**Table 1 clc23949-tbl-0001:** Patient characteristics at baseline

Age, years, *n* (%)
Female sex, *n* (%)
Height, cm
Weight, kg
Body mass index
AF type
Blood pressure, mmHg
Heart rate, /min
Congestive heart failure, n (%)
Hypertension, *n* (%)
Diabetes mellitus, *n* (%)
Stroke and/or transient ischemic attack, *n* (%)
Vascular disease, *n* (%)
Structural heart disease, *n* (%)
Coronary artery disease
Valvular heat disease
Dilated cardiomyopathy
Hypertrophic cardiomyopathy
Others
Post‐open heart surgery
NYHA class
Bleeding history or predisposition
Labile INR, *n* (%)
Concomitant aspiring or nonsteroidal anti‐inflammatory drugs
Excess alcohol use
CHADS_2_ score
CHA_2_DS_2_‐VASc score
HAS‐BLED score
Transthoracic echocardiographic data
LV ejection fraction, %
LV end‐diastolic diameter

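### Coagulation markers are sampled before and after ablation, but the only tests named for continuous variables are unadjusted, so an exploratory arm comparison of them would be less precise than it could be

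*Protocol article*

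**What the plan says.** Section 2.6.1 (Study procedures) lists prothrombin time, activated partial thromboplastin time, d-dimer, thrombin-antithrombin III complex, soluble fibrin monomer complex and DOAC blood concentration. It states that they "will be measured before the CA procedure as preoperative samples, and 1–3 days after the procedure". Each patient is therefore meant to supply a pre-procedure and a post-procedure value.

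Section 2.11 (Statistical analysis) gives one general rule for continuous variables. They are summarized by mean or median according to their distribution and "analyzed with the Student's *t*‐test or Wilcoxon rank‐sum test, as appropriate". The only regression models named have another purpose: "Logistic regression analyses and multivariable Cox regression analyses will be performed to investigate the predictors associated with clinical outcomes". The section also announces that "A detailed plan for the interim analysis and final analysis will be prespecified in the statistical analysis plan".

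The primary endpoint (section 2.3) is binary: "The primary endpoint of the Embo‐Abl study will be the occurrence of MRI‐detected SCEs 1–3 days after CA". The key secondary endpoints (section 2.4) include no coagulation marker. Table 2 has no row for these markers, and Table 1 has only a general laboratory line at baseline.

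**The concern.** When the same quantity is measured before and after an intervention, the pre-procedure value usually explains part of the between-patient variation in the later one. A two-sample test on post-procedure values leaves that variation in the error term. ANCOVA removes it, using samples that are already scheduled.

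This has some relevance here. The Discussion (section 4) names activation of the coagulation system among the possible sources of thrombotic debris. It also lists anticoagulant type and interrupted anticoagulation among reported, though disputed, risk factors. Section 2.6.1 lets DOAC handling follow each hospital's own practice, and minimization (section 2.9) covers only age, AF type and left atrial dimension. The pre-procedure marker value may carry part of the variation that comes from anticoagulation.

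What is at stake is the width of the confidence interval for an exploratory comparison of coagulation activation between CB and RF.

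**Working it through.** **The plan's own figure.** Section 2.8 states that "a rate of MRI‐detected SCEs of 20% in both groups is assumed", with a 15-point margin, 80% power and a 5% significance level, and arrives at 112 per group. The normal approximation gives

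n = (1.960 + 0.842)² × (0.2×0.8 + 0.2×0.8) / 0.15² = 7.849 × 0.32 / 0.0225 = 111.6, rounded up to 112.

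This reproduces the stated number with a one-sided 2.5% level (two-sided 5%); a one-sided 5% level would give 88. No marker enters this calculation, so nothing below changes 112, or the 115 per group to be enrolled.

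**Inputs for the marker comparison.** From the article: 115 per arm and 1:1 allocation. Set here: two-sided 5% and 80% power. Assumed, because the article does not give it: the pre/post correlation ρ, at 0.2, 0.3, 0.5 and 0.7. Also assumed: equal pre- and post-procedure SD, a linear relation, both samples available for everyone, and the one degree of freedom spent on the covariate ignored.

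**Residual variance relative to a t-test on post-procedure values.**
- Post-procedure value only: 1
- Change from the pre-procedure value: 2(1 − ρ)
- ANCOVA on the pre-procedure value: 1 − ρ²

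**Standard error and equivalent sample size, ANCOVA against post-only.**
- ρ = 0.2: √0.96 = 0.980, SE 2% lower; 1/0.96 = 1.04 times the patients
- ρ = 0.3: √0.91 = 0.954, SE 5% lower; 1/0.91 = 1.10 times
- ρ = 0.5: √0.75 = 0.866, SE 13% lower; 1/0.75 = 1.33 times
- ρ = 0.7: √0.51 = 0.714, SE 29% lower; 1/0.51 = 1.96 times

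**Minimum detectable difference, in SD units.** Post-only: (1.960 + 0.842) × √(2/115) = 0.369. The other columns multiply this by the square root of the variance factor.

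| ρ | Post-only t-test | Change-score t-test | ANCOVA |
|---|---|---|---|
| 0.2 | 0.369 | 0.467 | 0.362 |
| 0.3 | 0.369 | 0.437 | 0.352 |
| 0.5 | 0.369 | 0.369 | 0.320 |
| 0.7 | 0.369 | 0.286 | 0.264 |

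For a true difference of 0.369 SD, where the post-only test has 80% power, ANCOVA has 81.6%, 83.6%, 89.9% and 97.5% in the four rows.

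ANCOVA is the most precise of the three in every row. This follows from the factors: 1 − ρ² never exceeds 1, and 1 − ρ² = (1 − ρ)(1 + ρ) never exceeds 2(1 − ρ). A change score is worse than ignoring the pre-procedure value when ρ is below 0.5. These figures are for the t-test; the loss with the rank-sum test was not computed.

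**The case against.** The strongest reply is that the article plans no such comparison. The markers appear once, as a sampling step. They are not endpoints, have no row in Table 2, and might serve only as candidate predictors of cerebral embolism in the logistic models. The model for an exploratory laboratory variable is commonly left to an SAP, and section 2.11 announces one. All of this stands, and it is why the point is conditional and minor. It does not remove the point, because section 2.11 does state a rule for continuous variables, and an SAP that follows it would carry over the unadjusted tests.

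A reader might infer three stronger things that the article does not support.
- **That baseline information is thrown away.** Section 2.11 does not say whether the tests apply to post-procedure values or to changes, and a test on changes does use the pre-procedure value. The advice holds either way, since ANCOVA is at least as precise as both.
- **That the unadjusted comparison is biased by chance imbalance in markers or anticoagulation.** In a randomized comparison the unadjusted test is valid, and its standard error already allows for such imbalance. The issue is precision only.
- **That the loss is large.** The size rests wholly on an assumed ρ. For DOAC level and clotting times ρ may be low, because section 2.6.1 lets doses be continued or withheld and resumed at different times.

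It is also fair to object to log-scale ANCOVA as a remedy for every marker. DOAC concentration does not apply to patients on warfarin, may be near zero when a dose is withheld, and depends on dose timing.

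**Conclusion.** The point holds in a limited form. The one rule stated for continuous variables has no baseline covariate, although the pre-procedure marker values are scheduled. If CB and RF are compared on post-procedure markers under that rule, the estimate will be less precise than it could be: relative to a post-only t-test, the standard error would be about 2% to 29% lower with ANCOVA for ρ from 0.2 to 0.7. That range is an assumption, may differ between markers, and could be near its lower end. The stated analysis is not invalid. The primary endpoint, the noninferiority test, the 112 and 115 per group and the trial's power are unaffected. This is a worthwhile improvement at almost no cost, with medium confidence because the SAP is not shown.

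**What to change.** Add to section 2.11 or the SAP that any between-arm comparison of post-procedure coagulation markers will use ANCOVA of the post-procedure value on arm and the pre-procedure value. Use the log scale for skewed positive markers such as d-dimer, thrombin-antithrombin complex and soluble fibrin monomer complex. Report the adjusted difference, or the adjusted ratio on the log scale, with its 95% CI, in place of the unadjusted t-test or rank-sum test. Analyse DOAC concentration separately, in DOAC users only, with its own stated method. If no arm comparison of the markers is intended, say so; no change to the tests is then needed.

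The cost is wording only: no further samples, visits or patients. It should be settled before the SAP is finalized.
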